#### 3.1.2. Phase II: Qualitative Component (Discourse Analysis)

Secondary Outcome: To analyze the discourses and interpretive repertoires of nursing professionals in order to explore the symbolic barriers, latent biases, and institutional or organizational facilitators that cannot be captured by closed-ended instruments like the SABS scale.Secondary Outcome: To identify the key meaning structures within professional narratives that explain potential discrepancies between theoretical comfort and actual clinical practice, using these insights to explain and enrich the quantitative findings from Phase I through methodological triangulation.

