## 3. Objectives

The overall goal of this research project is to analyze whether differences exist in primary care nursing approaches to human sexuality counselling depending on whether the care is explicitly directed toward LGBTQ+ individuals or the general population.

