#### 3.1.1. Phase I: Quantitative Component (Pilot Cross-Sectional Survey)

Primary Outcome: To evaluate and compare self-reported attitudinal barriers and perceived comfort scores among primary healthcare nursing professionals when providing human sexuality counselling, as measured by the total and dimensional scores of the Sexuality Attitudes and Beliefs Survey (SABS).Secondary Outcome: To estimate the statistical relationship between these sexuality-related attitudes/beliefs and key sociodemographic and professional variables (specifically age, sex, years of experience in primary care, and previous training in sexual diversity).

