#### 4.2.3. Study Variables

Study variables include those related to the biopsychosocial characteristics of nursing professionals (age, sex, educational level, sexual orientation, primary care centre, employment type and years of experience in primary care) collected via an ad hoc questionnaire and the 12 items of the SABS scale (Table 1) [34].

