#### 4.2.4. Procedure, Sample Size and Data Analysis

The validated Sexuality Attitudes and Beliefs Survey (SABS) [34] will be used as the measurement instrument. The sample will be divided into two groups:Group A: Nursing professionals who complete the SABS scale with a brief introduction making specific reference to the sexual and reproductive care of LGBTQ+ individuals.Group B: Nursing professionals who complete the SABS scale with a brief introduction referring to the sexual and reproductive care of the general population, without specifying sexual orientation or gender identity.

Data collection procedure:Initial contact will be made with the heads of the health centres to inform them of the study objectives and obtain institutional consent. Following acceptance, cluster allocation will be performed to generate two groups (Group A and Group B). To ensure maximum methodological rigour, the cluster allocation sequence will be generated by an independent statistical researcher who is completely external to data collection and recruitment. The generation will be performed using a computerized random number generator. Allocation concealment will be maintained at the institutional level: health centres will be assigned to either Group A or Group B simultaneously, and participating nurses will be blinded to the existence of an alternative version of the survey, mitigating potential performance or social desirability biases.The SABS scale will be used to evaluate attitudes and beliefs around human sexuality in nursing, with the aim of detecting obstacles in sexual counselling and recommendations.

The complete survey comprised: (1) an ad hoc section collecting sociodemographic data (age, primary care centre, nationality, sex, sexual orientation, educational level, employment type, and years of experience in primary care), and (2) 12 SABS items rated on a five-point Likert scale (1 = Strongly disagree to 5 = Strongly agree). The survey will be distributed electronically via the LimeSurvey platform, with biweekly reminders to maximize response rates.

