#### 4.3.3. Procedure

In-depth semi-structured interviews will be used as the primary data collection technique. The interviews will be conducted by members of the research team who possess specific postgraduate qualifications and formal academic experience in qualitative health research and gender/LGBTQ+ perspective studies (specifically authors [name], [name]). A formalized, pre-tested interview protocol and semi-structured question guide will guide the process, ensuring consistency across participants while allowing space for emerging themes. The primary language utilized during the interviews will be Spanish, given the professional setting within the Andalusian Health Service; however, bilingual protocols (Spanish/English) will be available to accommodate potential diversity among participating healthcare professionals. As an optimization strategy to guarantee the authenticity of discourse and mitigate social desirability, the possibility of integrating clinical vignette elicitation will be considered, which involves presenting hypothetical scenarios to facilitate the projection of real attitudes.

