## 6. Conclusions

This study protocol outlines a necessary framework to identify and dissect institutional discrimination towards LGBTQ+ patients within the primary healthcare system. By thoroughly analyzing both the barriers and facilitators in nursing care, this research aims to expose the systemic gaps that compromise equity and quality in healthcare delivery for sexual and gender minorities. The anticipated findings are expected to underscore a critical, undeniable need: the implementation of specialized training programmes in sexual and reproductive health tailored for nursing professionals. Addressing this educational deficit is a vital step toward dismantling institutional biases and fostering culturally competent care. Furthermore, the strategic dissemination of the results—through high-impact journals, open-access repositories, and direct communication with participating primary care centres—will not only guarantee transparency but also establish a robust, empirical foundation to guide future research, healthcare policies, and intervention strategies in LGBTQ+ health equity.

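### A Phase II outcome sets stated comfort against actual clinical practice, but both phases collect only nurses' own accounts, so that gap cannot be established

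*Protocol article*

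**What the plan says.** Section 3.1.2 of the protocol article lists two outcomes for the qualitative phase. The second begins "To identify the key meaning structures within professional narratives" and continues that these structures are to "explain potential discrepancies between theoretical comfort and actual clinical practice". The results are then to be used to explain and enrich the Phase I findings by triangulation.

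The data sources are stated outright:

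- **Phase I.** The primary outcome (3.1.1) is to "evaluate and compare self-reported attitudinal barriers and perceived comfort scores". Section 4.2.3 describes nurse characteristics "collected via an ad hoc questionnaire and the 12 items of the SABS scale", and 4.2.4 confirms a sociodemographic section plus "12 SABS items rated on a five-point Likert scale".
- **Phase II.** Section 4.3.3 names semi-structured interviews with nurses as the main technique. On vignettes it says only that "the possibility of integrating clinical vignette elicitation will be considered", and describes them as hypothetical cases meant to draw out attitudes.
- **Integration.** Section 4.3.4 contrasts the discourse findings with the SABS results and asks why nurses who score well on competence show insecurity or avoidance in what they say.

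Section 6 describes the protocol as a framework to "identify and dissect institutional discrimination towards LGBTQ+ patients within the primary healthcare system".

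**The concern.** A discrepancy has two sides, and explaining one presupposes that both can be seen. Here one side is a questionnaire score, and the other is named as practice but is supplied by the nurse's own talk. If the outcome is reported under its present label, a mismatch between closed items and narrative, which are two forms of self-report, would be presented as a mismatch between what nurses say and what they do.

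Section 6 then invites the further step of reading that mismatch as evidence of discrimination in the care system. The same section expects the results to guide policy and intervention strategies, so the difference between narrated and delivered care affects how the findings would be used.

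**Working it through.** No formula applies, and the plan gives no figure to reproduce. The check is to take each stated data source and ask whether it carries information on care delivered that is independent of the nurse's own account.

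| Source | Where | Committed? | What it yields | Measures delivered care? |
|---|---|---|---|---|
| Ad hoc questionnaire and SABS | 4.2.3, 4.2.4, Table 1 | Yes | Nurse characteristics; 12 self-rated agreement items | No |
| Semi-structured interviews, 15–20 expected | 4.3.2, 4.3.3 | Yes | Nurses' narratives | No |
| Clinical vignettes | 4.3.3 | Only considered | Responses to hypothetical cases | No |

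Table 1 gives the same result line by line. It has 1 row for allocation group, 8 for nurse characteristics (sex, age, nationality, education, sexual orientation, centre, employment, experience) and 1 for the SABS: 1 + 8 + 1 = 10 rows, none of which describes a consultation.

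Other elements that might fill the gap do not:

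- Member-checking (4.3.4) tests whether the interpretation fits the participant's narrative. It does not test whether the narrative fits the care given.
- Direct observation, record review, simulated patients and patient reports are named nowhere.
- The limitations in section 5 acknowledge social desirability in self-report and offer the interviews as mitigation. Interviews are also the nurse's account. The text does not say that practice is unmeasured.

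Now set the outcome beside the analysis meant to deliver it:

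| | Side 1 | Side 2 |
|---|---|---|
| Outcome (3.1.2) | Theoretical comfort | Actual clinical practice |
| Analysis (4.3.4) | SABS scores | Interview discourse |

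The first side matches. The second does not. The analysis section describes a contrast that the interviews can supply, while the outcome names one that they cannot. The count is two committed sources, one optional source and no measure of practice.

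**The case against.** The strongest reply is that the outcome is interpretive. Its object is meaning structures in narratives, and interviews under discourse analysis supply those. The discrepancies are called potential, and section 4.3.4 already names its comparator correctly as discourse. The abstract and section 5 are also restrained, speaking of potential barriers, attitudes and perceived competencies. On this reading only one phrase is loose.

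Much of this stands. The narrative part of the outcome is answerable, and it would be wrong to say that the whole outcome fails. It does not rescue the phrase about actual practice, however. Calling the discrepancy potential leaves open whether a gap exists, and either answer needs information on practice. The accurate wording in 4.3.4 shows what the outcome should say; it does not remove the conflict between the two sections.

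A reader might infer two stronger points that the article does not support:

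- **That the overall goal has no measure behind it.** Section 3 aims to "analyze whether differences exist in primary care nursing approaches to human sexuality counselling", and approaches could be read as observed care. But 3.1.1 operationalises the goal at once as self-reported barriers and comfort, measured by SABS total and dimensional scores. The goal has a measure.
- **That vignettes should be made compulsory, in paired LGBTQ+ and unspecified form.** Responses to hypothetical cases would still not measure practice. That vignettes would be used in some interviews and not others is conjecture, since 4.3.3 commits to a formalised, pre-tested guide for consistency across participants. Showing one nurse both versions would also expose the contrast that 4.2.4 keeps hidden from nurses.

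**Conclusion.** The point holds for the second Phase II outcome as worded: a gap between comfort and actual clinical practice cannot be established from the planned data, so it cannot be explained. A gap between SABS-reported comfort and the practice nurses narrate can be described and interpreted with the planned interviews.

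Its reach is one of the two Phase II outcomes, which is a secondary and qualitative one, together with the discrimination claim in section 6. The primary outcome, the Group A versus Group B comparison, the sample size and the Phase II data collection do not change.

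The conclusion assumes that the article's list of data sources is complete. That is reasonable, because the sources are stated outright in both phases and nothing in the text points to a further source on care delivered.

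**What to change.** Make three changes of wording:

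1. In 3.1.2, restate the second outcome as *discrepancies between SABS-reported comfort and the practice nurses describe in interview*. This aligns it with the triangulation in 4.3.4.
2. In the limitations in section 5, add that delivered care is not measured in either phase, and that the interviews, like the SABS, give the nurse's own account.
3. In section 6, limit the claim from identifying institutional discrimination to barriers and attitudes as reported by nurses. The abstract already uses more cautious terms that could be carried over.

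The Data Availability statement says that data collection has not begun, so the changes can be made in advance. They need no new data, interview time or analysis. The price is narrower conclusions: the study could report where questionnaire answers and narrated practice diverge, but not how nurses behave in consultations.

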## 4. Materials and Methods

### 4.1. Study Design

This study will employ a sequential explanatory mixed-methods design (DEXPLIS). This design allows a quantitative panoramic view of perceived barriers to be obtained in a first phase (Phase I), followed by an in-depth exploration of the discourses, meanings and underlying biases of nursing professionals through a qualitative approach (Phase II). The quantitative component will be reported following relevant SPIRIT guidelines (Standard Protocol Items: Recommendations for Interventional Trials) where applicable.

### 4.2. Phase I: Pilot Quantitative Study

#### 4.2.1. Study Design and Study Population

Phase I consists of a pilot cross-sectional study with cluster allocation of questionnaire versions, in which primary healthcare nursing staff in the MVGHD will complete the validated Sexuality Attitudes and Beliefs Survey (SABS).

#### 4.2.2. Study Sample and Inclusion/Exclusion Criteria

Given the exploratory nature of this phase, the study is configured as a pilot and feasibility study. A total sample of *n* = 112 subjects is gathered via cluster allocation at the health-centre level. To justify the statistical validity of this sample size under a cluster design perspective, we consider a total of 33 health centres (clusters) with an estimated average cluster size of m approx 3.4 nurses. Assuming a conservative Intraclass Correlation Coefficient (ICC) of *p* = 0.02 for attitudinal measurements in primary care, the calculated Design Effect (Deff) is approximately 1.05 [Deff = 1 + (m − 1)*p*]. This indicates that the variance inflation due to clustering is minimal, confirming that the sample size of *n* = 112 retains sufficient statistical power for this pilot exploration while matching formal feasibility criteria.

Inclusion criteria: Nursing professionals currently working in primary care within the MVGHD who freely accept participation as indicated by the integrated informed consent within the survey.Exclusion criteria: Healthcare professionals performing functions outside the scope of community nursing or working in settings other than primary care.

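### A design effect of about 1.05 does not confirm sufficient power for n = 112; at the protocol's own ICC the detectable difference is about 0.54 to 0.57 SD

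*Protocol article*

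**What the plan says.** Section 4.2.2 of the protocol article states that "the study is configured as a pilot and feasibility study" and fixes the size: "A total sample of *n* = 112 subjects is gathered via cluster allocation at the health-centre level". The justification follows in three steps. The cluster structure comes first: "we consider a total of 33 health centres (clusters) with an estimated average cluster size of m approx 3.4 nurses". Next comes the correlation: "Assuming a conservative Intraclass Correlation Coefficient (ICC) of *p* = 0.02 for attitudinal measurements in primary care". Then the result: "the calculated Design Effect (Deff) is approximately 1.05", from the usual formula 1 + (m − 1) × ICC. The text calls the resulting variance inflation minimal and treats it as confirmation that the sample "retains sufficient statistical power for this pilot exploration while matching formal feasibility criteria".

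Elsewhere, section 3 makes the existence of a difference between the two framings the overall goal. Section 3.1.1 makes the comparison of SABS total and dimensional scores the Phase I primary outcome. Section 4.2.5 plans Mann–Whitney U tests for two-group comparisons, with a significance threshold of 0.05.

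**The concern.** The conclusion does not follow from the quantity computed. A design effect compares the clustered sample with an individually sampled one of the same size, so it gives the share of information lost to clustering. Whether the remaining information is enough depends on the difference of interest, the spread of the scores and the required power, and none of these enters the calculation. By the same reasoning, any sample size with small centres and a low ICC would be confirmed as adequate.

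What is at stake is the reading of a null result. The A-versus-B comparison is the main aim of Phase I and is to be tested at 0.05. If the study has been described as having sufficient power, a non-significant result could be taken as evidence that framing makes no difference, although small to moderate differences would often have been missed.

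**Working it through.** **Inputs from the article.** n = 112, 33 centres, m ≈ 3.4 and ICC = 0.02 (section 4.2.2); significance threshold 0.05 and Mann–Whitney U (section 4.2.5).

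**Assumptions, not in the article.** Two-sided test, 80% power, 1:1 split, full response, an analysis that respects the clustering, and results in SD units because no SD is given.

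**1. Reproduce the plan's figure.**
- 33 × 3.4 = 112.2, which agrees with 112.
- Deff = 1 + (3.4 − 1) × 0.02 = 1.048, so the stated 1.05 is correct.
- Information lost = 1 − 1/1.048 = 4.6%.
- Effective n = 112/1.048 = 106.9, or 53.4 per group.

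**2. Does a small design effect imply adequate power?** Set Deff = 1. The detectable difference at 80% power is (1.960 + 0.842) × √(4/112) = 0.53 SD. Removing clustering altogether barely changes the answer, so the sample size sets the limit and the design effect says almost nothing about it.

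**3. Detectable difference at ICC 0.02.** The standard error of the difference is √(4 × 1.048/112) = 0.1935 SD.

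| Basis | Detectable difference, 80% power |
|---|---|
| Normal approximation: 2.802 × 0.1935 | 0.54 SD |
| t, 110 df | 0.55 SD |
| Normal, Mann–Whitney efficiency: 0.542/√(3/π) | 0.55 SD |
| t, 31 df (33 centres − 2) | 0.56 SD |
| t, 31 df, with Mann–Whitney efficiency: 0.5595/0.977 | 0.57 SD |

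A split of 16 and 17 centres leaves the normal value at 0.54 SD.

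**4. Power at ICC 0.02.**

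| True difference | Normal | t, 31 df |
|---|---|---|
| 0.2 SD | 18% | 17% |
| 0.3 SD | 34% | 32% |
| 0.4 SD | 54% | 52% |
| 0.5 SD | 73% | 71% |
| 0.6 SD | 87% | 85% |

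On the normal approximation with Deff 1.048, 80% power would need about 132 nurses for 0.5 SD and about 367 for 0.3 SD. These totals show the scale of the gap; they are not a proposal to enlarge the study.

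**5. Illustrative sensitivity, all on the t (31 df) basis.** The ICC of 0.10 and the cluster-size coefficient of variation (CV) of 0.65 are chosen for illustration.

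| Case | Deff | Detectable difference |
|---|---|---|
| ICC 0.02, equal centres | 1.048 | 0.56 SD |
| ICC 0.10, equal centres | 1 + 2.4 × 0.10 = 1.24 | 0.61 SD |
| ICC 0.10, CV 0.65 | 1 + ((1 + 0.4225) × 3.4 − 1) × 0.10 = 1.38 | 0.64 SD |

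**6. Precision.** The expected 95% CI half-width is 2.04 × √(4 × Deff/112): 0.39 SD at ICC 0.02, and 0.45 SD in the last case of step 5.

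**The case against.** The strongest reply is that Phase I is a pilot and feasibility study, that a pilot need not be powered for a hypothesis test, and that power is claimed only for an exploratory purpose. The word *retains* can also be read modestly, as saying that clustering costs little of whatever power 112 nurses would have. That modest statement is true, as step 1 shows. What remains is that the article says more: it offers the calculation as justification of the sample size and draws from it a positive conclusion that power is sufficient, while testing the main comparison at 0.05. The pilot label would support dropping the power claim; it does not support making it.

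A second reply is that a journal article may leave the target difference, the SD, the derivation of 112 and the feasibility criteria to a fuller document. That stands. Their absence is not the point here; the point is an inference stated in the article itself.

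A third reply concerns the ICC. A reader might infer that 0.02 is too low, or that calling it conservative is wrong. The documents do not support this: they give no benchmark for nurse attitudes. The higher ICC in step 5 shows sensitivity and is not evidence against 0.02. Unequal centre sizes also matter little at the protocol's ICC: with CV 0.65, Deff is 1.08 and the t (31 df) figure moves only from 0.56 to 0.57 SD.

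Finally, the article does not say that a null result will be read as no difference. Its discussion speaks of preliminary evidence, and section 4.2.5 already plans effect sizes. The risk of misreading is therefore a possibility to guard against, not something the plan commits to.

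**Conclusion.** The point holds as a fault of inference and wording. The design effect of about 1.05 is correct, but it does not confirm sufficient power. At the protocol's ICC the design reaches 80% power only for differences of about 0.54 to 0.57 SD. On the t (31 df) basis a true difference of 0.3 SD would be missed about two times in three, and one of 0.4 SD about half the time. These figures rest on a two-sided 5% test, 80% power, a 1:1 split and full response; of these, the article gives only the 0.05 threshold. The range of 0.54 to 0.57 SD covers the choice of reference distribution and the efficiency of the Mann–Whitney test.

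A reader might go further and infer that 112 nurses are too few. That does not follow: the article names no difference that the study must detect, and a pilot can rest on feasibility or precision.

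**What to change.** In section 4.2.2, delete the statement that the design effect confirms sufficient power. It can still say that clustering is expected to cost under 5% of the information. Then take one of two routes:

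- justify n = 112 on feasibility or precision alone; or
- state the detectable difference with its assumptions (two-sided 5%, 80% power, 1:1 split, full response): about 0.55 to 0.57 SD at ICC 0.02 and, as an illustrative sensitivity on the t (31 df) basis, 0.61 SD at ICC 0.10 and 0.64 SD if cluster-size CV is also 0.65.

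Under either route, give the expected 95% CI half-width (about 0.39 SD at ICC 0.02, up to 0.45 SD in the less favourable case) and add that a non-significant result does not exclude smaller differences. Present the ICC of 0.02 as an assumption with a range around it.

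The change is to wording only, and the Data Availability statement indicates that data collection has not begun. No extra nurses are needed. The cost is a less favourable statement of what the study can detect.
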